### Who will take informed consent? {26a}

A 2-page study flyer is posted at the check-in desks of the treatment program’s outpatient and residential facilities. This flyer explains the study and provides contact information for the research coordinator and principal investigators. Additionally, research personnel review the opioid treatment program’s pregnancy census list weekly for new pregnant admissions or newly delivered clients. Staff at the opioid treatment program are asked to identify eligible individuals. All identified individuals are contacted by study personnel, either by phone or in-person, informed about the study, and asked if they are willing to participate. If they agree, an enrollment interview is carried out. Study personnel explain the purpose of the study, answer questions, and obtain written informed consent from those who meet study inclusion criteria. Those who consent to participate are provided with a copy of the consent form with contact details of the research team. Eligible individuals who do not agree to participate are asked to self-report basic sociodemographic information (e.g., age, education level, number of kids, and reason for refusal) to allow a comparison of enrolled and non-enrolled individuals. All staff responsible for obtaining consent are trained and certified in the protection of human subjects and study-specific consent procedures.

### Additional consent provisions for collection and use of participant data and biological specimens {26b}

When obtaining informed consent, participants are informed that their data will be de-identified and stored in a secure database and that any data released will not be identifiable. Participants will be told they can withdraw consent at any time during the trial. This trial does not involve collecting biological specimens. Data will not be used or distributed for future research studies.

## Interventions

### Explanation for the choice of comparators {6b}

The intervention is an adapted version of an existing, evidence-based model of group WCC (*CenteringParenting *[14]). Standard individual WCC is the comparator.

### Intervention description {11a}

As the framework for the group WCC intervention, we leveraged Centering®, a model of care delivery developed by The Centering® Healthcare Institute [15]. Centering® seeks to shift the paradigm of health services from individual to group care, bringing patients out of a traditional office and into a group setting where they learn from their providers and each other. Each group session has planned core content, with consistency of providers across all sessions, and 2 h per session for health assessment, interactive learning, and community building. Instead of didactic education, providers use facilitative leadership, encouraging patients to fully engage in their care and raise issues of importance to them.

*CenteringParenting*is the pediatric adaptation of Centering® and is based on the American Academy of Pediatrics recommended schedule of visit periodicity, including developmental milestone assessments, anticipatory guidance, and immunizations [16]. In addition to standard WCC topics focused on infant health and development, *CenteringParenting*places emphasis on maternal wellness including nutrition and exercise, family planning, stress reduction, and interpersonal relationships [14, 17].

Participants who enroll into CHAMPS during pregnancy and are randomized to the intervention arm initially receive routine individualized well care after birth hospital discharge. This consists of an initial 30-min newborn visit usually within 2–3 days after discharge at the affiliated pediatric primary care office, with any additional 15-min visits in the first few weeks of life as needed, i.e., for jaundice or a weight check. Beginning with the 1-month WCC visit, mother-infant dyads grouped by birth month (anticipated *n* = 3–5 per group) are scheduled for WCC together, with subsequent visits occurring at the American Academy of Pediatrics recommended intervals (2, 4, 6, 9, 12, 15, and 18 months of age). Group WCC visits occur on-site at the opioid treatment program. Infants with an extended hospitalization beyond 1 month are eligible to join into a later group session if needed.

Participants who are already parenting a child < 12 months of age at the time of enrollment and are randomized to the intervention arm are grouped with other mother-infant dyads by infant birth month and scheduled for WCC together. Group WCC visits occur on-site at the opioid treatment program. Visits occur at the American Academy of Pediatrics recommended intervals.

Group WCC sessions diverge from individual WCC in the following ways:*Setting and duration*: Group WCC sessions occur in a dedicated group room at the SUD treatment program and last 2 h. A room divider with a computer and an examination table offers a private area for pediatricians to examine the infant and review history, current issues, and other maternal concerns. The group space itself entails a circle of chairs or pillows on the floor with mats in the middle for infants. There are shelves with children’s books and toys that participants may use. Healthy snacks are provided during the session for the mothers and their children (when age appropriate).*Provider interaction*: Each group is assigned to one pediatrician who will lead all WCC sessions for that group, with a nurse practitioner from the opioid treatment program serving as co-facilitator. All providers involved in delivering group WCC are trained in group facilitation by Centering Healthcare Institute, which emphasizes skills such as reflective listening and strategic questioning as opposed to didactic education. A pediatric nurse assists with immunizations and other procedures.*Content*: A structured, reproducible modular curriculum guides session content, with flexibility based on group needs. Facilitated group discussions provide opportunity for skills building, knowledge sharing, and normalization of early parenting experiences. In addition to standard topics within the *CenteringParenting *curriculum, emphasis on specific clinical topics is tailored to the patient population. Topics were selected and prioritized based on the team’s collective experience as experts in OUD treatment and pediatric primary care and from results from the team’s formative qualitative research conducted with mothers with OUD and pediatric providers [7]. Aspects of Mindfulness Based Parenting [18, 19]—a relational approach developed from the principles of mindfulness and that calls for the full attention of parents when interacting with their children—is also incorporated into each session.*Scheduling*: Sessions are scheduled in advance to reoccur on consistent days and time in coordination with other scheduled groups at the opioid treatment program. Participants who no-show for group WCC are contacted to schedule a routine office-based individual visit. Participants in group WCC are able to schedule acute visits in the office as needed.

### Control description

Clusters randomized to the control arm receive routine individualized WCC at an urban, hospital-owned academic pediatric practice located 5 city blocks from the opioid treatment program. This practice site includes 14 physicians and nurse practitioners, serves a predominantly Medicaid-insured population, and is a training environment for students and residents. Newborns are scheduled for an initial 30-min visit within 3–5 days after discharge home, with any additional 15-min visits in the first few weeks of life as needed (i.e., for jaundice or a weight check). Subsequent 15-min WCC visits occur at recommended intervals per American Academy of Pediatrics recommendations (1, 2, 4, 6, 9, 12, 15, 18, 24, 30, and 36 months of age). Routine care in this practice setting includes maternal depression screening, provision of books as part of a national literacy promotion program, developmental screening, and social determinants of health screening. A dedicated RN coordinator tracks receipt of preventative services for all patients and provides outreach to patients who no-show for WCC, and access to subspecialty care, social work, and lactation services are available on-site. Scheduling of visits may occur in-person at the registration desk, through an online patient portal, or by telephone. Phone or text appointment reminders are provided the day before scheduled visits.

### Criteria for discontinuing or modifying allocated interventions {11b}

Patients can leave the study at any time for any reason if they wish to do so without any consequences. Following a live birth, participants will remain eligible to continue in the study unless the mother and/or infant experiences the following: gestational age at time of delivery less than or equal to 32 weeks or illness or clinical complication warranting prolonged hospitalization after delivery. Even when a participant randomized to the intervention does not receive the intervention, we will attempt to complete the follow-up data collection to ensure a complete dataset.

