### Trial design {8}

This is a single-site cluster randomized controlled trial. One hundred eight pregnant and parenting women receiving treatment for OUD from one single opioid treatment program will be enrolled into the study. Twenty-six consecutive clusters—based on the one-month birth intervals of participants’ infants—of ~ 4 dyads will be randomized in a 1:1 ratio to one of two study arms. Thirteen clusters will be randomized to individual WCC (control group), and 13 birth clusters will be randomized to group WCC (intervention arm), with concealment of randomization from participants until after they have completed their initial enrollment study visit, or, for those who are pregnant at time of enrollment, immediately following delivery. Randomization by birth month was selected to ensure a close age range among infants receiving group WCC together in the intervention arm. Blocking or stratification was not used in the randomization. Dyads in both study arms will be followed prospectively for 18 months, and data will be compared between the two study arms. Primary outcomes include well child care quality and utilization, child health knowledge, and parenting quality. We hypothesize that at the end of the study period, participants in the intervention arm will have increased WCC engagement, knowledge about parenting, and maternal responsiveness compared to participants in the control arm.

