### Concealment mechanism {16b}

As an open-label study, both participants and researchers know about the assignment of participants to the treatment groups. The treatment assignment sequence was forwarded to the principal investigator of the project after generation.

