## Statistical methods

### Statistical methods for primary and secondary outcomes {20a}

#### Quantitative data

Analyses will follow intent-to-treat principles, with participants analyzed according to randomized treatment assignment of the cluster in which they reside. Most analyses will use the individual participant as the unit of analysis, but because randomization is at the cluster level, model-based approaches that account for the correlation between individual participants within a cluster will be used.

Collected data will be summarized in tabular and graphic forms. Demographics and other study variables will be summarized by treatment groups. Mean (SD) or median (interquartile), as appropriate, will be used to describe numerical data, and frequency and percentage will be used to describe the distribution of categorical variables between treatment groups. Two-sample t-test, Mann–Whitney U test, chi-square test, and Fisher’s exact test will be used to compare the distribution of study variables between two-intervention groups as appropriate. Longitudinally collected data will be summarized by intervention groups and data collection time points.

Analysis of variance (ANOVA) and generalized linear and logistic regression models will be used to analyze outcomes measured at one time point, as appropriate. Trajectories of change for outcomes that are repeatedly measured over time will be examined using generalized linear mixed models (GLMMs) and linear, logistic, and negative binomial/Poisson regression models for continuous, binary, and count outcomes. Total scores and subscales from assessments will be used when applicable. The use of GLMM models will allow for an estimation of between-group differences in outcomes at each time point of measurement and will allow for an estimation of changes over time and time by group interactions while accounting for within-subject associations arising from the repeated measures. Clustering of participants will be accounted for in the GLMMs models by including cluster as a random or fixed effect and in the generalized models by using robust variance estimates. Potential covariates will be selected based on consideration of study arm balance and potential confounders for an outcome previously reported in the literature.

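### The rule that ends participation for prolonged hospitalization conflicts with the intervention text, is judged with the arm known, and undercuts the intention-to-treat analysis

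*Protocol article*

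**What the plan says.** All references are to the protocol article.

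- **Criteria for discontinuing or modifying allocated interventions {11b}.** Once a child is born alive, a dyad may no longer carry on in the trial if mother or infant meets either limb of this condition: "gestational age at time of delivery less than or equal to 32 weeks or illness or clinical complication warranting prolonged hospitalization after delivery". No length of stay is attached to the second limb. The section closes with a safeguard: "Even when a participant randomized to the intervention does not receive the intervention, we will attempt to complete the follow-up data collection".
- **Intervention description {11a}**, in the paragraph on women who enroll during pregnancy: "Infants with an extended hospitalization beyond 1 month are eligible to join into a later group session if needed".
- **Trial design {8}.** The cluster is the infant's month of birth. The arm is withheld from participants until after the initial enrollment visit or, "for those who are pregnant at time of enrollment, immediately following delivery".
- **Concealment mechanism {16b}.** "As an open-label study, both participants and researchers know about the assignment of participants to the treatment groups". The sequence went to the principal investigator once it had been generated.
- **Quantitative data, under {20a}.** "Analyses will follow intent-to-treat principles, with participants analyzed according to randomized treatment assignment of the cluster in which they reside".
- **Eligibility criteria {3}.** Women may enter from 28 weeks of pregnancy or with a child under 12 months. No entry criterion refers to gestational age at birth or to hospitalization.

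**The concern.** Sections {11a} and {11b} give different answers for the same infant. A stay of more than a month after birth would ordinarily be called prolonged, so {11b} ends participation while {11a} expects the infant to appear at a later session.

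The timing makes this more than an editorial slip. Whether a stay is prolonged can be judged only some time after delivery. By then the birth month has fixed the arm, and staff and mother both know it. An undefined criterion applied with the arm known leaves room for different decisions in the two arms, even if nobody intends it.

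The dyads concerned are plausibly those with the greatest health-care needs. If their participation ends, their outcomes are not collected, and an analysis described as intention-to-treat rests on a set selected after allocation.

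**Working it through.** **1. Do the two sections cover the same dyads?** The sentence in {11a} sits in the paragraph on women enrolled in pregnancy. Section {11b} speaks of what happens following a live birth, which most naturally means the same women. The overlap is infant stays beyond 1 month, and there the conflict is direct. Section {11a} is silent on maternal hospitalization, on shorter stays that someone might still call prolonged, and on gestational age. For birth at 32 weeks or earlier, the conflict with {11a} is therefore only indirect, through the long stays that may follow.

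**2. Is the arm known when the judgement is made?**
- Gestational age is settled at delivery and leaves nothing to judge.
- Birth month is settled at delivery, and with it the cluster and the arm ({8}).
- The principal investigator already holds the sequence, and the trial is open label ({16b}).
- The participant is told immediately after delivery ({8}).
- A prolonged stay becomes apparent only later, and {11b} names neither a length nor an assessor unaware of the arm.

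Arm-driven selection is thus possible for the hospitalization limb and unlikely for the gestational-age limb.

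**3. What is lost when a dyad leaves soon after birth?** Under Outcomes {12}:

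| Primary outcome | When measured |
|---|---|
| Well child care utilization | Total over 18 months |
| Care experience (PHDS) | 6, 12 and 18 months |
| Parenting knowledge | 18 months, and change from baseline |
| Interaction quality (KIPS) | 18 months |

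Such a dyad has no post-baseline value for the last three and a truncated count for the first. The promise in {18b} to use partial data from dropouts cannot restore what was never collected.

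**4. Sample-size figures reproduced (section {14}).**
- Enrollment: 150 × 0.90 × 0.80 = 108, or 54 per arm. There is no term for removals after delivery.
- Detectable difference, normal approximation: (1.96 + 0.84) × √(2/54) = 0.539. The t-test version gives 0.544. Both agree with the stated 0.54.
- Power at 0.54 with 54 per arm: 80.1% (normal) or 79.4% (t-test).

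**5. Illustration of removals.** The documents give no rate, so the fractions below are assumptions. They apply to both arms equally, with n = 54 × (1 − fraction), a t-test, two-sided 0.05 and no allowance for clustering.

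| Assumed removal | n per arm | Power at 0.54 | Detectable difference at 80% power |
|---|---|---|---|
| 0% | 54 | 79% | 0.54 |
| 5% | 51.3 | 77% | 0.56 |
| 10% | 48.6 | 75% | 0.57 |
| 15% | 45.9 | 73% | 0.59 |
| 20% | 43.2 | 70% | 0.61 |

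These fractions are of all dyads, whereas the rule appears to reach only women enrolled in pregnancy, whose share is not stated. If they were half of the sample (a further assumption), an overall 5% to 20% would require removing 10% to 40% of them, since 0.05/0.5 = 0.10 and 0.20/0.5 = 0.40. The upper rows are therefore a generous bound.

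**The case against.** The case for leaving the text alone has real force.

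- **The rule in {11b} is worded for participants in either arm.** The sentence in {11a} can be read as scheduling: an infant who misses the first session may start at a later one. Control infants have no group to join, so the control description needs no matching sentence. This stands. A reader might infer that sick infants stay in the intervention arm and leave the control arm, and might attach a bias to it: if 10% of controls were removed and they scored 0.5 SD worse than the rest, the control mean would rise by 0.10 × 0.5 = 0.05 SD. The documents do not support that reading. No section says that the arms are treated differently, and both inputs are invented.
- **Section {11b} concerns continuing in the study and does not define the analysis set.** This also stands, so it would be too strong to say that the plan excludes these dyads from the intention-to-treat analysis. The practical problem remains, because a dyad whose participation ends brings almost no primary outcome data to that analysis.
- **The same section promises follow-up when the intervention is not received.** This helps only in part. The promise names participants randomized to the intervention, has no counterpart for controls, and is not said to cover dyads who have ceased to be eligible.
- **A condensed article may leave the length of a prolonged stay to the full protocol.** That is fair for the definition, and a threshold well above 1 month could narrow the conflict. No such threshold is printed, and the two printed statements disagree as they stand.
- **The gestational-age limb is harmless.** Largely so. It is objective, fixed at delivery, and cannot be influenced by group visits that begin at 1 month. It still removes dyads after birth and has no counterpart in {3} for mothers who enroll when already parenting. That is an inconsistency between enrollment routes, and nothing links enrollment route to arm.

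**Conclusion.** The point holds for the hospitalization limb. Sections {11a} and {11b} conflict on infants with long stays and must be reconciled; which clinical rule applies is for the investigators. The judgement is made after allocation, on an undefined criterion, with the arm known. Ending participation on that basis loses the 18-month outcomes of dyads who belong in the promised intention-to-treat comparison.

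The gestational-age limb adds a loss of dyads and an inconsistency between enrollment routes, but little risk of arm-driven selection.

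The size cannot be calculated from the documents. Under an assumed 5% to 20% removal from both arms, the unclustered detectable difference would move from 0.54 to between 0.56 and 0.61, and power at 0.54 would fall from about 79% to between 77% and 70%. That is a modest cost in precision. Any bias would depend on how discretion was exercised in each arm, on which the documents say nothing. The conclusion rests on the text and would stand whatever the removal rate.

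**What to change.** 1. Reconcile {11a} and {11b} into one rule, worded identically for both arms, on what happens after a prolonged hospitalization. If the term is kept, define it.
2. Separate receiving the assigned form of care from staying in the study. State that every dyad whose cluster has been allocated stays in follow-up, at minimum through abstraction of the medical record unless consent is withdrawn, and remains in the intention-to-treat set in both arms whether or not sessions are attended. Extend the follow-up promise in {11b} to control participants.
3. If the gestational-age criterion is kept, treat it as an eligibility check made at delivery and recorded before the arm is disclosed to the participant. Dyads who fail it would be the only exception to item 2 and should be counted by arm. Staff may still infer the arm from the birth month, so the protection comes mainly from the criterion being objective. State also whether it applies to mothers who enroll when already parenting. Recording before disclosure cannot work for prolonged hospitalization, which is not known at delivery; item 2 is the remedy there.
4. Report by arm any dyads already removed under the present wording and, where consent still stands, abstract their records to 18 months.

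The cost is a short amendment with IRB approval, some extra abstraction for what may be a small number of dyads, and slightly more outcome variability from keeping sicker infants. Utilization already comes from the medical record, so that outcome needs no new instrument.

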### Strategies to improve adherence to interventions {11c}

We will use multiple strategies to retain the study sample over the duration of the study. These strategies include (1) providing reminders calls before visits; (2) limiting participant burden by scheduling visits when participants are already attending the treatment program for medication dispensing or therapy; (3) paying for car ride services (e.g., Uber) and providing vouchers for parking lots for participants to use while they are completing study visits; and (4) sharing information about the study with opioid treatment program staff and providers across the hospital system (e.g., Neonatology, General Pediatrics, Ob/Gyn).

